## Background

Young people (aged 16–24) in the UK report higher levels of unprotected sex than any other age group and are also at highest risk of sexually transmitted infections (STIs) [1]. STIs are associated with socio-economic inequality [1] and early intervention is required to prevent disadvantage converting to poor lifetime sexual health. Young people’s elevated risk has been linked to lack of awareness, insufficient knowledge of how to protect themselves, and social norms that denigrate safer sexual behaviour and undermine the quality of intimate relationships [2].

Students in school represent a ‘captive audience’ and schools are particularly well placed to reach disadvantaged young people at higher risk of adverse sexual health outcomes, and before sexual attitudes and behaviours become entrenched [3]. Young people who cite school as their main source of information about sex are less likely to report unsafe sex and previous STI diagnosis [4]. The proportion citing school as their main source is increasing [5], but the content and quality of provision of sex education in UK schools is variable [6]. Over two thirds of young people report inadequate knowledge at the time they first felt ready to have some sexual experience [5], suggesting significant room for improved delivery of school-based sex education.

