### Sample size and selection

As a feasibility study, STASH is not designed to identify an estimate of effect and thus a standard power calculation is not appropriate. Allowing for non-response of 15% due to student absence, the sample size across all six schools is approximately 700 intervention participants and 700 controls. This should be sufficient to allow qualitative and quantitative progression criteria to be assessed and provide information on key parameters for the design of a future trial. It is premature to specify the required sample size for a future trial but is nevertheless useful to have a broad indication of the likely size of such a trial. It is anticipated that a full trial would be cluster randomised, with school as the unit of randomisation. Assuming a mean school year size of 150 students and an effect size of 0.1, then a trial of between 15 and 25 schools per arm would have 80% power across a range of scenarios in which (1) intra-cluster correlation is assumed to be either 0.01 or 0.03, (2) there is one or two primary outcomes, and (3) follow-up rates vary between 75% and 85%.

Schools will be recruited via local authority education services. STASH project staff will initially contact school management teams by email and meetings will be arranged with those expressing interest. Follow-up emails and calls will be made as necessary. Response rates, and any stated reasons for non-participation, will be recorded. Schools will be recruited on a first come, first served basis, while keeping mindful of the need to ensure variation in terms of school size, geographic location and area deprivation.

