The feasibility of recruitment of schools to cluster randomised trials has been well established in many previous trials, so we have opted to implement the intervention in all six study schools, rather than recruit a larger number of schools and randomise half to the control. The prior cohort of S4 students (i.e. those completing S4 in the year prior to the intervention) in each school will complete the outcome questionnaire towards the end of their academic year (and prior to implementation of the intervention in the subsequent cohort of S4 students) and their data will be compared with the cohort of S4 students participating in the intervention. Therefore, the prior cohort of S4 students will serve as controls who received usual provision of sex and relationships education, which in most Lothian schools is a version of the Sexual Health And Relationships Education (SHARE) package [24].

Schools will be considered formally recruited to the study on the administration of the control questionnaire and signature of the research contract by a senior staff member. Any school opting to discontinue with the study after this point will be considered a withdrawal.

To maximise retention, schools will be given £500 to compensate for disruption to school life due to the questionnaire and process evaluation activities, plus £500 to compensate for staff time taken up by intervention activities (e.g. staff attendance at training).

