		RED: Amber target achieved in fewer than 4 schools	Indication of doubt as to whether to proceed. Recommend as per red target for Criteria 1		
3	Was STASH acceptable to stakeholders and target group?	GREEN: In each of 4 schools, 60% of students who are exposed to STASH agree that the intervention was acceptable. No major acceptability issues raised by participating schools (identified via process evaluation or communication with school) Less than 15% of peer supporters report that parents were unhappy about them being a peer supporter	Very strong indication to proceed	Follow-up Questionnaire Process evaluation interviews Peer Supporter questionnaire	We consider 60% a reasonable target given the sensitivity of the topic. 60% represents a majority and is realistic in the context of a feasibility study. Acceptability to teachers and school leadership will be assessed qualitatively, hence a focus on identification of major issues rather than a quantitative target.
		AMBER: In each of 4 schools, 50% rate intervention as acceptable Less than 20% of peer supporters report that parents were unhappy about them being a peer supporter One or two major acceptability issues raised by participating schools but mitigating strategy identified	Medium indication to proceed. Recommendation as per amber target for Criteria 1		
		RED: Amber target achieved in fewer than 4 schools Major acceptability issues raised by schools with no possible mitigating strategy	Indication of doubt as to whether to proceed. Recommendation as per red target for Criteria 1		
4	Were the evaluation methods acceptable and feasible?	GREEN: In each of 4 schools, student response rates of >70% at baseline and follow up	Very strong indication to proceed	Baseline and Follow-up Questionnaires	We consider a response rate of 70% sufficient to undertake analysis, and feasible given that this cohort are undertaking public examinations at the end of the year. Response rates in the pilot were lower than expected for a school survey. Parental opt out has been very low and nearly all students in attendance complete the questionnaire, but due to the age group (and linked to area deprivation) there are students who are regularly absent (e.g. because they also attend other services).
		AMBER: In each of 4 schools, student response rates of >60%	Medium indication to proceed. Recommendation as per amber target for Criteria 1		

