#### Baseline characteristics

Baseline characteristics (including deprivation) will be summarised overall and by study group (intervention/control) and for those who were and were not followed up (or dropped out of intervention). Exploratory investigations of the associations between baseline characteristics and successful follow-up may be carried out using appropriate statistical tests and mixed effects logistic regression models (to reflect the clustered nature of the data by school), to identify potential sources of bias in future studies.

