#### Outcome data

Outcome data will be summarised overall and by study group. Mixed-effects regression models, with a random effect for school, will be used to estimate the magnitude of intervention effects with 95% confidence intervals. The effects of individual-level factors (effect modifiers) potentially associated with outcomes will be explored by extending these regression models, to identify key trial design parameters in future studies. Interaction models may be considered to explore whether the intervention might be more or less effective (or inferior) for particular subgroups of students. The within-school intra-class correlation coefficients will be reported for each outcome and used to inform sample size calculations for the future RCT. The study is powered for exploratory analysis only and so analyses will not be testing hypotheses regarding intervention effectiveness. Missing data will not be imputed since this is a feasibility study.

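### The reported STASH effect should be adjusted for deprivation and other pre-exposure characteristics, because a change between years in who answers the survey can appear as part of it

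*Protocol article*

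**What the plan says.** Under Sample size and selection, the previous S4 cohort in the same six schools acts as the control, and "their data will be compared with the cohort of S4 students participating in the intervention". The Outcome data section gives the model: "Mixed-effects regression models, with a random effect for school, will be used to estimate the magnitude of intervention effects with 95% confidence intervals". It then allows individual-level factors to be added by extending these models, with the stated aim of finding design parameters for future studies. The Effect modifiers list shows that these factors include IMD and free school meal status. On missing data it says: "Missing data will not be imputed since this is a feasibility study".

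On who responds, the rationale for criterion 4 in Table 1 reports that those who are present almost always fill in the survey. It puts the shortfall down to absence: "due to the age group (and linked to area deprivation) there are students who are regularly absent". The Background notes that "STIs are associated with socio-economic inequality". The Baseline characteristics section plans a summary by study group, including deprivation. It also allows optional modelling of who was followed up, "to identify potential sources of bias in future studies". The Outcome data collection section calls the two cohorts comparable on the ground that both are surveyed at the same point in the school year.

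**The concern.** The contrast is between two year groups that were not randomised and were surveyed a year apart. By the article's own account, the students most likely to be absent are more often from deprived areas. A random effect for school handles differences between schools. It does nothing about a change, within a school, in which students answered from one year to the next.

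If deprived students responded less in the intervention year than in the control year, and their risk is higher, STASH would look somewhat protective with no true effect. If the shift ran the other way, STASH would look harmful. The 95% interval reflects sampling error and would not show either.

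The neighbouring provisions do not deal with this as worded. The extended models serve another purpose. The follow-up model cannot describe control non-respondents, because controls are surveyed once. Criterion 4 is assessed on the baseline and follow-up questionnaires and does not cover the control survey.

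**Working it through.** **The plan's own figure.** "Allowing for non-response of 15% due to student absence, the sample size across all six schools is approximately 700 intervention participants and 700 controls". Working back, 700 / 0.85 = 824 eligible students, or 824 / 6 ≈ 137 per school. The year sizes of the six schools are not given, so 700 cannot be checked. The mean of 150 is stated for the future trial only; it would give 6 × 150 × 0.85 = 765. Nothing below depends on this.

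**Inputs for the distortion.** The article gives no risk by deprivation, no deprived share and no response by stratum. All of these are assumed: deprived share *s* of 20% to 40%; risk in deprived v other students of 35% v 25% (10-point gap) or 40% v 20% (20-point gap); and several response patterns. The true effect is set to zero.

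**Formula.** The deprived share among respondents is s·r_dep / [s·r_dep + (1 − s)·r_oth]. The spurious difference is the risk gap × (that share in the intervention year − that share in the control year).

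Example with s = 40%, a 20-point gap, and response (deprived/other) of 80%/87% in controls and 40%/87% in the intervention year:
- Controls: 0.320 / (0.320 + 0.522) = 0.380.
- Intervention: 0.160 / (0.160 + 0.522) = 0.235.
- Difference: 20 × (0.235 − 0.380) = −2.9 points.

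Results in percentage points, as ranges over s = 20% to 40%:

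| Response, deprived/other: control → intervention | 10-point gap | 20-point gap |
|---|---|---|
| 70/90 → 70/90 (same pattern) | 0.0 | 0.0 |
| 80/90 → 65/75 (similar fall in both) | −0.04 to −0.06 | −0.07 to −0.12 |
| 70/90 → 50/90 | −0.41 to −0.71 | −0.82 to −1.42 |
| 75/90 → 45/85 | −0.56 to −0.96 | −1.11 to −1.93 |
| 80/87 → 40/87 | −0.84 to −1.45 | −1.68 to −2.91 |

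**Case with overall response near 85% v 70%.** These are the planning figure and the green limit of criterion 4. Take s = 30%, risk 35% v 20%, and response 75%/89% v 45%/81%.
- Overall response: 0.225 + 0.623 = 84.8% in controls and 0.135 + 0.567 = 70.2% in the intervention year.
- Deprived share among respondents: 0.225 / 0.848 = 26.5% and 0.135 / 0.702 = 19.2%.
- Difference: 15 × (0.192 − 0.265) = −1.1 points.

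**Scale.** At 700 v 700 and an assumed prevalence of 30%, ignoring clustering, the 95% half-width is 1.96 × √(2 × 0.3 × 0.7 / 700) = 4.8 points.

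**What adjustment does.** Within each deprivation stratum the assumed risk is the same in both years, so a deprivation-adjusted contrast is zero by construction. A simulation agrees (300 runs, six schools, 137 students per school and cohort, true effect zero, school intercepts fitted as fixed). With risk 40% v 20% and response 80%/87% v 40%/87%, the school-only model gave −2.1 points, and adding deprivation gave +0.2, about zero within simulation error. When absence in the intervention year depended on the outcome itself (response 30 points lower among those with it), the results were −7.7 points without deprivation and −7.4 with it.

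**The case against.** The strongest reply is that the choice of covariates and of the main model normally belongs to the SAP, which is not shown, and that this article is condensed. The next sentence of the section does extend the models with the factors in question. A summary by study group, including deprivation, would reveal a shift in composition. Mop-up visits reduce absence, and the control survey is expected to inform response rates. All of that stands. What remains is that the article does state which model estimates the effect, and gives the extension a different purpose. The summary and the mop-up visits correct nothing in the estimate.

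Three stronger readings are tempting, and the documents do not support them:
- *Unequal response by itself produces a false effect.* It does not. A similar fall in both strata moves the contrast by about 0.1 point at most. The pattern by deprivation must differ between the years, and nothing in the article shows that it does.
- *The no-imputation sentence is the error.* An absent student supplies no questionnaire data, so imputation would not readily repair whole-survey non-response. The weakness is the missing adjustment.
- *A false effect could drive the decision to proceed.* None of the four criteria in Table 1 uses the effect estimate, and the article says that effectiveness hypotheses will not be tested.

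A larger distortion can be obtained by assuming that non-respondents differ from respondents by 20 or 30 points. At 85% v 70% response this gives 0.15 × 20 = 3.0 or 0.15 × 30 = 4.5 points. Deprivation does not support gaps of that size: in the 85% v 70% case above, the implied gaps are only 3.4 points (controls) and 5.4 points (intervention). Nor should the result be expressed as a share of the effect in "Assuming a mean school year size of 150 students and an effect size of 0.1", because that figure belongs to the future trial and its scale is not stated.

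**Conclusion.** The point holds as a modest one. As described, the reported cohort contrast can absorb a change between years in who responded, and the protocol's own account of absence makes deprivation the obvious route.

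The distortion is zero if the response pattern is the same in both cohorts. If the drop is concentrated in deprived students, it is about 1 to 3 points with a 20-point risk gap and about 0.4 to 1.5 points with a 10-point gap, inside a half-width of about 4.8 points. Every share, risk and differential response rate here is assumed. The Background sentence concerns STIs, so even the risk gap for the questionnaire outcomes is an assumption.

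The estimate is exploratory and does not feed the progression criteria. The change is worth making because the better analysis uses data already being collected and costs almost nothing.

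**What to change.** In the Outcome data section:

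1. Make the reported cohort contrast the mixed model with the school random effect plus fixed main effects for pre-exposure characteristics collected in both cohorts: gender, IMD, free school meal status, ethnicity and religiosity. Show the unadjusted estimate beside it.
2. Report response by school and cohort, including the control survey, next to the effect estimates.
3. State that adjustment removes only the part of differential non-response explained by these covariates. Optionally add one sensitivity analysis that shifts non-respondents' outcomes by a stated range in each cohort, for example 5 to 20 points.

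The no-imputation rule can stay. If the SAP already specifies the adjusted contrast, one sentence saying so is enough.

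The cost is some plan wording and a little extra analysis, with no new data, schools or students. The downside is that students with a missing covariate need a 'not known' category or drop out of the adjusted model.

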#### Analysis for economic evaluation

We will conduct an initial cost-consequences analysis reporting descriptive statistics for the exposed and unexposed groups separately. Statistics will include data completeness and percentage that each resource contributes to total costs. This will inform areas where additional information may be needed in a full trial for more accurate costings. Costs will include the cost of peer supporter training and teacher time associated with STASH in the intervention group and sexual health resource use (STI testing, treatment and contraception) multiplied by published unit costs for both groups. QALYs will be calculated as the area under the curve using student responses to the CHU9D at the two time-points. The responsiveness of the CHU9D to the primary outcome and other hypothesised mechanisms of change will also be evaluated. Descriptive statistics will be reported for questionnaire completion alongside means, standard deviations and bootstrapped 95% confidence intervals by exposed/unexposed group for each variable**.** This will form the basis of a cost-consequences analysis, reporting costs alongside consequences such as QALYs and measures of behavioural change for intervention and control groups. As per the outcome analysis, missing data will not be imputed.

#### Qualitative analysis

The qualitative analysis will take a thematic analytic approach informed by the Framework method [37]. A focused coding framework will be developed and applied to interview transcripts and ethnographic observational notes. The framework will be strongly informed by the programme theory as well as the aims of the feasibility trial (fidelity, acceptability, exposure, reach, context, recruitment and retention), while also mindful of emerging issues not anticipated by the research team.

Following this categorising stage, the data will then be examined across sources (students, teachers, trainers) and cases (schools), to explore commonalities and differences in accounts of the trial, to develop potential explanations for these and to better understand the functioning of the intervention. A subsequent integrative analysis will be conducted to bring together key components of the qualitative and quantitative data. Integrative analysis involves placing all relevant data in one integrative matrix and assessing for synergy and will focus on assessing the overall feasibility of the intervention.

#### Social network analysis

Social networks exert important influences on health behaviour, including among adolescents [38] and we wish to contribute to the understanding of how these networks operate. These data will enable the identification of the extent of friendships outside the school, and therefore estimate potential contamination in a full-scale cluster randomised trial, and will assess the reach of the peer supporters across the S4 year group. Social network analysis will provide us with new ways of investigating how offline and online interactions are shaped and sustained by relational mechanisms. In particular, they will enable identification of clusters, of individuals considered particular trustworthy, of ‘information hubs’ (measures of centrality [39]), as well as isolated individuals (no nominations). The analysis will help to highlight whether perceived trustworthiness overlaps with the peer supporter role (are the most trusted individuals also the most active peer leaders?). We plan to investigate homophily, i.e. whether subgroups of the network are formed around gender (e.g. do girls only talk to girls?), sexual behaviour (do high-risk individuals mainly talk to other high-risk individuals?), norms (are those who voice specific opinions largely connected to others with similar opinions?) and other node characteristics.

#### Participant information and informed consent

A senior staff member from participating schools will be asked to sign a research contract outlining the responsibilities of the school and the researchers. Prior to the start of the intervention phase, S4 students and their parents will receive an information sheet telling them about the STASH study. Informed opt-in consent from the students will be required for all specific components of the research study, including questionnaires (opt-out for parents), interviews and focus groups and from the peer supporters and their parents for them to participate in the training and take on the peer supporter role. Parental opt-out consent for the questionnaire is important since research over many years shows that the lower participation with opt-in consent is strongly biased away from the most vulnerable young people [40].

At all study stages, participants will be informed that they can withdraw from any research component at any time without prejudicing their experience at school. Research participants will be reassured that their answers will be treated in confidence. Researchers will only break confidentiality if a disclosure in a face-to-face interview suggests that a young person might be at risk of serious harm or of harming others. The intervention website will include links to local and national referral services.

#### Procedures for reporting harms and safeguarding issues

The STASH research team will employ strategies to minimise the likelihood of untoward incidents with potential to cause harm. This includes behavior such as inappropriate/inaccurate posting, online bullying and breaches of private information by peers.

At the training, peer supporters will be required to sign up to a code of conduct (the STASH Charter). Social media use will be confined to private (‘secret’, ie. non-visible, invite-only) Facebook groups, of which a STASH trainer will be a member. Trainers will conduct monitoring ‘spot checks’, and peer supporters will also be encouraged to report any untoward incidents promptly to the trainer and/or STASH contact teacher. Students will also have the option to privately message the trainer as required. In line with STASH study procedure for reporting harms, the trainer should pass on any concerns to the contact teacher without delay. Procedures for dealing with disrespectful/aggressive online behaviour will follow the information and communication technologies (ICT) code of conduct and discipline code of participating schools.

Appropriate responses to sensitive disclosures and procedures for reporting potential child protection issues will be explained—and their importance emphasised—during the 2-day peer supporter training. In particular, peer supporters will be advised on how to respond to sensitive information shared by peers (including respecting privacy) and when to share these with the STASH contact teacher/Designated Member of Staff (DMS). Peer supporters will be advised that any disclosures about which they feel worried or uncomfortable should be reported without delay to the contact teacher/DMS. Schools have in place procedures for handling disclosures relating to child protection, which should then be followed as normal. Peer supporters are advised that they may also contact the STASH trainer via Facebook, if they wish (see below).

The STASH contact teacher/designated staff member and those delivering the intervention (STASH trainers and peer supporters) will be asked to notify the research team within five working days if any harm occurs to a member of staff or student, as a direct result of taking part in the STASH trial. Members of the research team will be required to document any harms reported to them during trial data collection. These will be discussed with the principal investigators, triaged according to severity and reported the Trial Steering Committee and funders as appropriate.

